## Abstract

**Background:**

The clinical onset of borderline personality disorder (BPD) usually occurs in young people (aged 12–25 years) and commonly leads to difficulty achieving and maintaining vocational (education and/or employment) engagement. While current psychosocial interventions lead to improvements in psychopathology, they have little effect upon functioning. Individual Placement and Support (IPS) is a client-driven model that assists individuals with severe mental illness to engage with education and/or employment appropriate to their personal goals, and that provides ongoing support to maintain this engagement. The objective of the INdividual Vocational and Educational Support Trial (INVEST) is to evaluate the effectiveness of adding IPS to an evidence-based early intervention programme for BPD, with the aim of improving vocational outcomes.

**Methods/design:**

INVEST is a single-blind, parallel-groups, randomised controlled trial (RCT). The randomisation is stratified by gender and age and uses random permuted blocks. The interventions are 39 weeks of either IPS, or ‘usual vocational services’ (UVS). Participants will comprise 108 help-seeking young people (aged 15–25 years) with three or more *DSM-5* BPD features and a desire to study or work, recruited from the Helping Young People Early (HYPE) early intervention programme for BPD at Orygen, in Melbourne, Australia. All participants will receive the HYPE intervention. After baseline assessment, staff who are blind to the intervention group allocation will conduct assessments at 13, 26, 39 and 52 weeks. At the 52-week primary endpoint, the primary outcome is the number of days in mainstream education/employment since baseline. Secondary outcomes include the cost-effectiveness of the intervention, quality of life, and BPD severity.

**Discussion:**

Current treatments for BPD have little impact on vocational outcomes and enduring functional impairment is prevalent among this patient group. IPS is a targeted functional intervention, which has proven effective in improving vocational outcomes for adults and young people with psychotic disorders. This trial will investigate whether IPS is effective for improving vocational (employment and educational) outcomes among young people with subthreshold or full-syndrome BPD.

**Trial registration:**

Australian New Zealand Clinical Trials Registry, ID: ACTRN12619001220156. 13 September 2019.

## Background

Borderline personality disorder (BPD) is a severe mental disorder that is characterised by difficulty managing interpersonal relationships, an unstable sense of self, intense and volatile emotions and impulsive behaviours [1]. The clinical onset of BPD usually occurs between puberty and young adulthood (‘young people’; aged 12–25 years) [2]. From this age, BPD is associated with substantial and enduring impairments in social and occupational functioning [3–6]. While these impairments are associated with characteristics of BPD, such as impulsivity [7], prospective studies have consistently found that functional impairment persists long after the diagnostic features of the disorder have attenuated [8–11].

BPD in young people predicts the persistence of functional impairments into adulthood [5, 6]. The severity of BPD features at age 14 is associated with lower academic and occupational attainment 20 years later [6]. Personality disorder severity at age 24 years is associated with the absence of post-school qualifications, receipt of disability welfare payments, and relationship difficulties at age 35 years [5]. Young people, aged 15–18 years, who experience severe mental illness, including BPD, are three times more likely to be disengaged from education than their peers in the general population [12]. Failure to begin tertiary education is associated with being not in education, employment or training (NEET) among 19–25 year olds [13] and, in one study of young people at entry into a specialist BPD treatment programme, 62% were either partially or fully NEET [14].

The enduring effects of early vocational disruption in this group are evident, with BPD more strongly associated with unemployment and impairment at work than depression or anxiety [15]. BPD features are consistently linked with impaired work performance, with even the presence of subthreshold features (1–4 *Diagnostic and Statistical Manual of Mental Disorders, version 5* (*DSM-5*) criteria) being associated with impaired work performance in a population sample of 18–64 year-olds [16].

Among outpatients aged 15–25 years, subthreshold features of BPD were associated with poorer occupational functioning than among those with no BPD features [17]. Of all personality disorders, BPD is the most strongly associated with receipt of disability welfare payments [18, 19], and people with BPD are more than eight times more likely to be receiving disability welfare payments than individuals with no personality disorder [19]. Over a 10-year follow-along period, people with BPD were three times more likely to be receiving disability welfare payments than those with other personality disorders [20]. Although 40% of those BPD patients were able to cease reliance on disability welfare payments at some point, almost half of those who ceased subsequently resumed benefits [20]. At the 10-year assessment, only 55% of the study population reported having worked or attended school for at least half of the previous 2 years. Consequently, BPD is among the most costly mental disorders [21], with indirect (decreased or lost productivity), rather than direct (treatment-related), costs accounting for the majority of the costs attributable to BPD [22–24].

Despite wanting to work in the open labour market [25], people with BPD struggle to maintain employment, and they find the experience of working more stressful than individuals with other mental disorders [26]. While improvements in psychopathology are observed following psychological intervention [27], this does not translate into substantial or sustained improvements in functioning [8]. For example, BPD patients treated with 1 year of dialectical behavioural therapy (DBT) showed no improvement in occupational functioning following treatment, or at 1-year follow-up [24].

BPD patients identify employment as helpful for recovery [25]. Self-reported effects of employment among those experiencing mental ill-health include improved self-esteem and self-worth, societal acceptance, and increased optimism [28]. Further, employment is viewed as a benchmark of recovery in those experiencing mental illness [29], including among young people recently diagnosed with a severe mental disorder [30, 31]. Lack of employment can have adverse consequences upon well-being [32], exacerbating the stigmatisation so commonly experienced by individuals with BPD. Unemployment at a young age also has ‘scarring’ effects, making future unemployment more likely [33, 34]. Therefore, specialised and targeted vocational support appears to be necessary to optimise recovery among young people with BPD and to prevent long-term disability.

Individual Placement and Support (IPS) has been specifically designed to provide vocational support for people living with severe mental illness (i.e., psychotic disorders) [35]. It is a client-driven model, delivered by a vocational specialist, that allows for ongoing personalised support, even after a suitable placement has been obtained. IPS has consistently proved more effective than other employment services in randomised controlled trials (RCTs) in countries with varying labour markets, economic conditions and attitudes towards mental health [32, 36–42]. IPS, inclusive of educational support, has been implemented successfully in young people experiencing first-episode psychosis [43–46]. While IPS has been adapted for use in other mental disorders among young people [47], no RCT has investigated its effectiveness among young people with BPD.

### Aims and hypotheses

The overall purpose of the INdividual Vocational and Educational Support Trial (INVEST) is to evaluate the effectiveness of IPS for improving vocational (educational and/or occupational) outcomes for young people with either subthreshold (three to four features) or full-syndrome (five or more features) BPD, compared with routinely offered, usual vocational services (UVS) within a specialist BPD outpatient programme.

The primary hypothesis is that, at the 52-week primary endpoint, participants receiving IPS will have better outcomes on the primary (number of days in mainstream education/employment since baseline) and secondary (cost-effectiveness of the intervention, quality of life, BPD severity) outcome measures than those receiving UVS.

## Methods/design

### Study design

INVEST is a single-blind, parallel-groups RCT of IPS, compared with UVS. The study design was developed in accordance with Good Clinical Practice (GCP) Guidelines and Standard Protocol Items: Recommendations for Interventional Trials (SPIRIT) [48]. Figure 1 summarises the trial design. Proposed or necessary changes to the protocol will be submitted to Melbourne Health Human Research Ethics Committee for approval, and communicated to all relevant parties. The trial was prospectively registered with the Australian New Zealand Clinical Trial Registry (ACTRN12619001220156) and has been approved by the Melbourne Health Human Research Ethics Committee (HREC/18/MH/257). The trial is funded through a project grant awarded by the National Health and Medical Research Council, Australia (GNT1144022).

**Fig. 1 Fig1:**
[figure not shown]
Consolidated Standards of Reporting Trias (CONSORT) flow diagram for the INdividual Vocational and Educational Support Trial (INVEST)

### Setting

All study participants will receive standard care in the Helping Young People Early (HYPE) clinical programme [49] at Orygen, Melbourne, Australia. Orygen is the Victorian State Government-funded specialist mental health service for 15- to 25-year-olds residing in western metropolitan Melbourne, Australia. HYPE integrates general psychiatric care, clinical case management, and time-limited, individual psychotherapy within an overall relational framework (Relational Clinical Care) that is derived from Cognitive Analytic Therapy (CAT) [50]. This treatment package is typically delivered over a period of 6–7 months. Patients are then offered up to four follow-up appointments over the subsequent 6 months, allowing adequate time to complete IPS or UVS.

HYPE provides a standardised background clinical treatment for all INVEST participants. HYPE adherence and competency are routinely monitored, at least weekly, through clinical supervision and clinical review processes. Individuals randomised to the IPS group will have contact with an IPS practitioner over the 39-week intervention period, in accordance with IPS principles.

The study will be conducted by Orygen and the Centre for Youth Mental Health, The University of Melbourne. Orygen, Melbourne, Australia is the study sponsor.

### Participants

Participants will be recruited from the HYPE programme at Orygen, Melbourne, Australia. Potential participants will be identified by case managers, referred to the research team and invited to participate in the study.

#### Inclusion criteria

Young people (all genders) aged 15–25 years inclusiveThree or more BPD features, assessed by the Structured Clinical Interview for *DSM-5* Personality Disorders (SCID 5-PD)A desire to enter mainstream education and/or employment (in which they are not currently engaged)Ability to give informed consent and adhere to study protocolSufficient fluency in English

#### Exclusion criteria

Participation interferes with the appropriate clinical management of risk of harm (or actual harm) to self or othersParticipation in another clinical trial which, in the opinion of the principal investigator, might confound the trial results

### Enrolment, randomisation and retention

Interested participants will complete the informed consent process with a member of the research team. This involves full written and verbal presentations of the study information, with all participants providing written, informed consent prior to commencement of formal study screening and eligibility confirmation. For potential participants aged under 18 years, a parent or legal guardian will be included in each stage of this process. Details of complaints and compensation procedures, and contact information for research personnel are included in the participant informed consent form. In addition to study consent, participants will be asked if they consent to their data being used for future research, and if they consent to being contacted for future research opportunities. Participants can opt in or out of one or both of these and still participate in INVEST.

Once eligibility for the trial is confirmed, the trial coordinator will randomly and consecutively assign participants to receive 39 weeks of either IPS or UVS, in a ratio of 1:1, using a password-protected computer programme, with a randomisation sequence that is computer-generated. Randomisation uses permuted blocks and is stratified by gender (female/not female) and age (< 18 years/18–25 years).

A graduate research assistant (RA) will conduct initial screening and will determine eligibility (in consultation with the study coordinator and principal investigator). The RA will also conduct all research assessments at 13, 26, 39 and 52 weeks. Intervention group assignment will be concealed from the RA (single-blind) conducting the assessments and from the biostatistician conducting the primary analyses. Blinding of the RA will be achieved and maintained by frequently reminding clinicians of the importance of the blind, excluding the RA from all clinical discussions, and forbidding the RA from accessing participants’ medical records. Any cases of un-blinding will be documented and another ‘blind’ RA will conduct assessments thereafter. Blinding of the RAs will be tested at the end of their employment or the end of the study, using an online self-report instrument designed specifically for the study. Study investigators will not be blind to group allocation, and the nature of the intervention precludes concealment from participants or clinicians.

Recruitment and retention in the trial will be maximised with thorough training of study RAs, including study-specific and GCP training. A comprehensive participant-tracking database will be utilised, and research assessments will take place on site at Orygen, at the participant’s home, or in the community, according to participant preference. Whether or not an individual chooses to participate in the trial will have no bearing on the clinical care that they receive in HYPE.

### Interventions

All participants will receive treatment in the HYPE programme at Orygen. This has been published elsewhere [49] and is comprised of general psychiatric care, clinical case management, and up to 16 sessions of individual psychotherapy where indicated. The programme is delivered within an overall relational framework (Relational Clinical Care), derived from CAT. Treatment received (i.e., number of sessions, case management v CAT) will be captured for each participant.

### IPS

IPS is a client-driven intervention that will be delivered by a qualified and fully trained IPS practitioner. The IPS practitioner identifies the employment and/or education goals of each individual and provides ongoing support to the young person, even following engagement in appropriate employment/education. IPS practitioners also provide support (education, advice, etc.) to workplaces and educational institutions, in order to facilitate and maintain the engagement of the young person. IPS was developed as an evidence-based employment services model for people with severe mental illness [51]. Since IPS was originally developed for adults with mental illness, a modified version of the intervention will be used. Modified IPS models, to include education, have been implemented successfully overseas [43, 44, 47], and within Orygen [52]. The model has eight core principles:
*Competitive employment and mainstream education*. The main aims of IPS are to help job seekers find employment in the open labour market and to help clients with educational goals find suitable educational programmes in mainstream institutions. IPS practitioners do not help clients find unpaid internships or sheltered employment*Eligibility based on client choice*. Involvement in an IPS service is based on a desire to achieve vocational goals in a competitive job or mainstream education. Clients are not excluded on the basis of diagnosis, disability or symptoms*Integration of vocational services and mental health services*. IPS providers and mental health treatment teams are closely integrated and work collaboratively*Attention to client preferences*. Services are based on individual client preferences. IPS practitioners actively approach employers and educational institutions based on the young person’s career preferences rather than referring to mismatched opportunities that employers need filled. Decisions regarding education and employment are based on client strengths, interests, and what they may have done in the past and previously enjoyed*Personalised benefits counselling*. IPS practitioners provide or help find accurate and understandable information about the effects that work will have on the job seeker’s welfare payments*Rapid job search*. IPS providers start looking for employment opportunities immediately rather than providing lengthy assessments, training and counselling. IPS practitioners work with clients in the first session to develop a vocational plan based on client preferences, past experiences, interests, skills and strengths*Targeted job development*. IPS practitioners build employment and educational provider networks and relationships through systematic contacts guided by client preferences. IPS practitioners form relationships by developing an understanding of each business and its human resource needs, explaining to hiring personnel what IPS is, and the benefits for participating businesses/institutions*Ongoing individualised support*. IPS clients can continue to receive support for as long as they require. IPS practitioners continue ongoing support long after a placement is found. Frequent contacts between employment specialists and clients are important to help with any required training and difficulties faced in the new environment

In the current RCT, ongoing individualised support from the IPS practitioner (principle 8) will cease at 39 weeks from baseline. The IPS practitioner will work with each participant to develop an individualised support plan, which might include case managers, family members or other service providers. This deviation from the model is necessary to maintain IPS practitioner caseload and study recruitment at acceptable levels. Time-limited IPS is comparable to traditional IPS in terms of employment outcomes [53], and 6 months of IPS has proven successful in assisting young people with first-episode psychosis to find employment [54] and to engage with education [52].

Adherence to the IPS model will be assessed using the IPS fidelity scale [55], which will determine the extent to which the IPS intervention is delivered according to the prescribed model. INVEST will utilise a modified version of the IPS fidelity scale designed to capture both educational and employment information, specifically for young people, ensuring a realistic measure of model adherence with the study population.

Each participant randomised to IPS will be assigned an IPS practitioner and will receive IPS services in accordance with the IPS fidelity scale. The un-blind study coordinator will provide relevant participant information to the IPS practitioner following randomisation and facilitate contact between specialist and participant. The IPS practitioner will meet with the participant as soon as possible, within 14 days following randomisation, to establish the participant’s short- and long-term vocational goals. Suitable employment/education opportunities will be identified, after which the IPS practitioner will provide support and advice regarding applications, writing a curriculum vitae, preparing for interview, and accompanying clients to interviews when this is the client’s preference. Sessions and contact with the IPS practitioner will vary in terms of length and communication method, but ongoing support will be provided as required or requested by the participant. Method of communication (e.g. telephone, face to face), length of interaction, and topics discussed will be recorded for each interaction between the IPS practitioner and participant. A participant will be considered discontinued from the intervention in the event of five failed contact attempts within a 1-month period or if a participant chooses to cease their involvement with the intervention. In the event of discontinuation, participants will still be permitted to provide research data if desired.

### UVS

UVS reflects the vocational support that is routinely available via case managers for young people attending the HYPE programme at Orygen. This includes the following educational support, offered in conjunction with Travancore School – a Victorian Department of Education and Training school providing education to those aged 15–18 years, while engaged with mental health services:
*Work it out (pathways planning).* A young person meets with a Travancore teacher and their case manager to discuss vocational goals and provide career pathway planning and support*Secondary consultation*. A Travancore teacher provides educational information and advice to the young person’s case manager, and family where appropriate. A secondary consultation does not include any school visits or educational setting liaison*Outreach*. A Travancore teacher offers outreach support to young people in a current education setting, or transitioning to a new setting*School’s in*. Learning support is provided within a small-group setting to a young person who wishes to re-engage with education

Employment support is not offered as part of UVS at Orygen. Case managers inform young people that this type of support can be obtained through Centrelink and/or employment agencies, and refer to such agencies. Centrelink is the Australian Government Department of Human Services programme that delivers payments and services for the unemployed, people with disabilities, students and apprentices. HYPE case managers have no specialised training or expertise in education networks, employment seeking or workplace support.

### Outcome measures at the primary endpoint

#### Primary outcome

The primary endpoint of the trial is 52 weeks after baseline assessment. Assessments will also occur at 13, 26 and 39 weeks after baseline.

The primary outcome is the number of days spent in mainstream education and/or employment since baseline. Because some study participants might engage in both education and employment during the course of the intervention, the number of days spent in each of education and employment will be separately recorded. To capture these data as accurately as possible, participants will receive the following two text-messages each week:
‘Orygen research. Think about the past 7 days, not including today. On how many days did you attend work or employment for which you were paid?’‘Orygen research. Think about the past 7 days, not including today. On how many days did you attend secondary school, education or training, working towards a qualification (for example VCE, VCAL, Certificate, Diploma, Degree, etc)?’

Participants will reply to each message with a number only (0–7). In order to compensate for any missed messages/non-responses, participants will be asked at each research assessment how many days they have attended education/employment in the past 13 weeks. The mean, minimum and maximum of the total numbers from the text-messages and the research assessments will all be considered in the analysis.

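### The two weekly texts bound, but cannot give, the number of distinct days in mainstream education and/or employment, and no rule for combining them is stated

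*Protocol article*

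**What the plan says.** Under Primary outcome the protocol article defines one quantity: "The primary outcome is the number of days spent in mainstream education and/or employment since baseline". Because some participants might do both activities, it adds that "the number of days spent in each of education and employment will be separately recorded".

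The two weekly texts are printed there. The first asks "On how many days did you attend work or employment for which you were paid"; the second asks "On how many days did you attend secondary school, education or training, working towards a qualification" and gives examples of qualifications. Each refers to the past 7 days and is answered with one number from 0 to 7.

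To make up for missed texts, "participants will be asked at each research assessment how many days they have attended education/employment in the past 13 weeks". The analysis is then to consider the totals from texts and assessments through their mean, minimum and maximum. What goes into a total is not defined.

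Statistical methods applies one t test to the primary outcome.

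**The concern.** Days in education and/or employment reads naturally as calendar days with at least one of the two, so at most 7 a week. Two separate counts do not show how many days held both, and a later analysis plan cannot recover what was never asked.

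The outcome is also limited to mainstream settings, and neither text carries that limit.

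At stake is the meaning of the variable in the main test. The IPS section describes support for both work and study, while the UVS section says that employment support is not part of UVS. Combining the two may therefore be more common under IPS, so a rule that handles overlap badly need not affect both arms equally.

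**Working it through.** **Inputs.** a = reply to the work text and b = reply to the education text, each a whole number from 0 to 7 (Primary outcome). The article gives no frequency of weeks with both activities and no standard deviation (SD) for the outcome, so there is no figure of the plan's own to reproduce here. The sample-size statement is not needed for the argument.

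**1. Bounds.** Let c be the days with both activities. Distinct days = a + b − c, and c lies between max(0, a+b−7) and min(a,b). Hence max(a,b) ≤ distinct days ≤ min(7, a+b).

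| a | b | lowest | highest | plain sum |
|---|---|---|---|---|
| 3 | 0 | 3 | 3 | 3 |
| 2 | 3 | 3 | 5 | 5 |
| 3 | 4 | 4 | 7 | 7 |
| 5 | 5 | 5 | 7 | 10 |
| 7 | 7 | 7 | 7 | 14 |

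**2. Which replies settle the answer.** There are 8 × 8 = 64 reply pairs. The bounds coincide only if a reply is 0 (15 pairs) or 7 (15 pairs), with 2 pairs in both sets: 15 + 15 − 2 = 28. The other 6 × 6 = 36, every pair with 1 to 6 days of each, leave a range. This counts possible replies; it does not predict how often they occur.

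**3. Over the year.** Replies of 2 and 3 in all 52 weeks give 52 × 3 = 156 to 52 × 5 = 260 days, a gap of 104. This is an extreme case, to show scale.

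**4. If the counts are summed.** The score exceeds the distinct days by c each week. The sum is above 7 for 28 of the 64 pairs and can reach 52 × 14 = 728 over 52 × 7 = 364 days.

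**5. Possible effect on the comparison, if summed.** Spurious difference = (excess share of IPS participants combining) × (weeks) × (overlapping days a week). All values here are assumed:
- no excess: 0 days
- 0.2 × 26 × 1 = 5.2 days
- 0.2 × 26 × 1.5 = 7.8 days
- 0.3 × 39 × 2 = 23.4 days

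With an assumed SD of 60 to 90 days, the design effect of 0.62 is 0.62 × 60 = 37.2 to 0.62 × 90 = 55.8 days. The two middle cases are then about 9% (5.2/55.8) to 21% (7.8/37.2) of it, and the last is 42% (23.4/55.8) to 63% (23.4/37.2).

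**6. Mainstream.** The IPS principles tie the aim to the open labour market and mainstream institutions, and state that "IPS practitioners do not help clients find unpaid internships or sheltered employment". The work text requires only pay, so paid sheltered work fits it. The education text requires only work towards a qualification, so qualification study outside a mainstream institution fits it. One UVS component run with Travancore School is described thus: "Learning support is provided within a small-group setting to a young person who wishes to re-engage with education". The article does not say whether such days count.

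**The case against.** The strongest reply is that this is a condensed article, and that the rule for combining the counts may stand in the full protocol or the analysis plan. That is fair as to the rule. It does not help with overlap: the texts are printed in the article, and no rule can recover which days coincided. Nor does the analysis of mean, minimum and maximum, which as worded compares totals across sources. The 13-week recall is presented as a back-up for missed texts, and as described it specifies neither distinct days nor mainstream settings.

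Other parts of the reply stand:
- In a week with only one activity, or none, the count of distinct days is exact.
- The texts already require pay or work towards a qualification, which screens out some non-mainstream activity.
- A reader might infer that reporting Travancore sessions works against IPS. The Discussion says that all participants continue to draw on usual vocational services, so those sessions are open to both arms and no direction is shown. Travancore also serves only ages 15–18, while the trial enrols ages 15–25, and use of vocational supports is recorded at each assessment.
- If IPS changes neither work nor study patterns, randomisation gives no systematic difference in overlap. The risk is mainly inflation of a real effect.

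**Conclusion.** The point holds as a defect in the stated data collection for the primary outcome. In any week with 1 to 6 days of each activity, the outcome is known only to lie between max(a,b) and min(7,a+b), and mainstream status is not asked. This rests on reading the outcome as distinct calendar days, which is the natural sense of and/or but is not spelled out.

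A reader might infer that the plan counts days with both twice. The article does not say so: it states no combining rule, and double counting follows only if the counts are summed. A reader might also infer a bias towards IPS of known size. The direction is conditional on IPS leading more participants to combine work and study, and the days worked out above rest wholly on assumed inputs. Nor can it be said that the score fails to measure the outcome in general, since weeks with one activity are measured exactly. The share of weeks affected is unknown.

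**What to change.** - **Add a third weekly text and use it for the primary outcome**, for example: *In the past 7 days, on how many days did you attend either paid work or education? Count a day with both once.* Keep the two existing counts as components.
- **Put the mainstream limit into the text wording**, and state whether Travancore programmes and paid sheltered work count.
- **Ask the 13-week recall question in the same way.**
- **For weeks already collected, report the primary comparison under both max(a,b) and min(7,a+b).** The lower bound alone should not be the main result: it scores 2 work days and 3 separate study days as 3 instead of 5, and so would work against whichever arm combines more. Applying one rule to both arms does not strictly bracket the difference between arms; the outer limits come from the lower bound in one arm and the upper in the other.
- **If a sum of activity-days is what is meant**, the outcome definition should say so.

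The cost is one more automated text a week and slightly more burden on participants. The Study design section requires protocol changes to go to the ethics committee for approval, so an amendment is needed. Trial status gives the first enrolment as 2 October 2019, so participants already enrolled would have a mixed instrument.
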